### Study procedure and design

The study and treatment will be conducted by the Department of Child and Adolescent Psychiatry, Psychosomatics and Psychotherapy Tübingen, Germany, a university hospital. The design of the study is open label for the therapists who will treat the patients and blinded for the diagnostician. Emergency unblinding will only happen for dropouts or severe cases. All procedures and the data security concept were evaluated by the Ethical Committee of the Medical Faculty of the University of Tübingen with the vote 639/2018BO1 dated 09/18/2018 (participant information, consent form, and data security concept are available from the authors upon request). All assessors who are involved in the study are trained psychotherapists (including a 3-year training after university studies of psychology/pedagogics). They also have profound training in diagnostics and statistical analysis. To maintain the scientific qualification, courses in Good Clinical Practice are to be completed regularly for all evaluators and study members.

In a telephone screening for eligibility by our study team (all experienced psychotherapists), participants are informed about the procedures. The enquiries received by the study team by phone or email will then processed by the treating therapists and contact will be made with the interested parties. If the inclusion criteria are met, an initial interview and a diagnostic appointment including introduction into the technical procedures will be arranged. Participants will get clinical questionnaires to fill out at home. Parental and children consent for study participation will be obtained in written form during the diagnostic appointments, which are conducted by a psychologist at the department face-to-face.

The participants will be assigned to the treatment or waiting group by block randomization according to the order of incoming calls. The randomization list is computer-generated and randomized to assign subjects to both groups in equal proportions. The randomization list was developed by our Institute for Clinical Epidemiology and Applied Biometry (IKEaB) with 8 blocks of 6 participants, consisting of *n* = 3 participants as waiting group and *n* = 3 participants starting treatment directly. The diagnostic expert will be blinded to the group condition. The assignment of the subjects will be pseudonymized by the randomization list, so that the diagnostician does not know which child is assigned to which group. The randomization list will be stored in a sealed envelope in the cabinet. After the patients are assigned to either the waiting or treatment group by block randomization according to the sequence of calls and inclusion in the study, they receive feedback on the allocation from a therapist from our study team. For this purpose, the therapist looks into the sealed envelope containing the order of the randomization list. This feedback is given either by telephone call or in person during the meeting on site at the clinic.

In the treatment condition, there are 14 weekly teleconference psychotherapy sessions lasting approximately 90 min each. Post-assessment will take place face-to-face. A total of 16 weeks after the treatment, there will be a first follow-up with clinical questionnaires that are sent to the families and a teleconference-based diagnostic session. A second follow-up will take place after another 16 weeks to further evaluate the effects and to enable comparing of the progress between treatment and waiting list group.

For the treatment group, outcomes will be evaluated before randomization (baseline, t0), after 16 weeks (end of treatment, t1), 32 weeks after randomization (follow-up I, t2), and 48 weeks after randomization (follow-up 2, t3). For the waiting list group, outcomes will also be measured before the first randomization (baseline, t0), at 16 weeks (waiting list period, t1), at 32 weeks (end of treatment, t2), at 48 weeks after the first randomization (follow-up I, t3) (compare Fig. 1), and at 64 weeks after the first randomization (follow-up II, t4).

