The documentation of the follow-ups including questionnaires will be recorded manually in the respective patient folders and kept locked in the cabinets in the clinic. If participants do not at all adhere to the protocol, are not motivated, or want to quit the study, they will drop out of the study; however, this will be the last option and motivational work will be done in advance. All planned outcomes will, nevertheless, be assessed for dropouts. A digital list of dropouts is kept within the study team and we note the reason for their dropout. Information about non-compliance, problems, or harms are continuously documented during the trial after every treatment session.

Data collection is monitored by our study team who meets every week. If problems with data collection become obvious, the team decides together about required next steps to ensure data quality, e.g., telephone call with the participants to encourage data completion. There is no external supervision of the data. As we use a low-risk intervention, there will be no trial auditing. As mentioned, the project team meets every week to discuss trial conduct.

There are no planned interim analyses that might lead to trial finalization. Trial would be stopped only if the team observes severe clinical reasons to stop the trail. These are, however, not expected because of our preliminary study and the fact that treatment is based on state-of-the art therapy methods. Data are in part only evaluated when needed, for example to show first preliminary results in presentations on conventions. If there are any changes to the protocol, these are discussed within the study team and the sponsor and changes are documented. If the protocol must be changed, the trials registry ClinicalTrials.gov will be updated. Only the study team has access to the final dataset.

Results will be disseminated in scientific papers, presentations in conventions, or within the university hospital or public media. Additionally, the funder will be informed about the results.

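### Dropout is a stated ground for unblinding, yet dropouts are still rated, so some t1 CY-BOCS scores could be rated unblinded and enter the primary comparison

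*Protocol article*

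**What the plan says.** All references are to the protocol article.

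- **Who is blinded.** Study procedure and design describes the trial as "open label for the therapists who will treat the patients and blinded for the diagnostician". After randomisation, of the families, it says "they receive feedback on the allocation from a therapist from our study team". The randomisation paragraph repeats that the diagnostician does not know the children's groups.
- **When the blind may be broken.** "Emergency unblinding will only happen for dropouts or severe cases". The sentence does not say who is unblinded, what makes a dropout an emergency, or whether the outcome is rated first.
- **What happens after dropout.** Later in the same section: "All planned outcomes will, nevertheless, be assessed for dropouts".
- **What is rated and compared.** Primary outcome names the clinician-administered CY-BOCS, compared between groups at t1 (week 16).
- **Which data are analysed.** Where data are missing, Statistical analysis reports on all the data that are available.
- **Related text.** For the treatment condition, "Post-assessment will take place face-to-face", and the first follow-up includes "a teleconference-based diagnostic session". On use of accumulating data: "Data are in part only evaluated when needed, for example to show first preliminary results in presentations on conventions".

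**The concern.** The primary outcome is a clinician's judgement, and the comparator is a waiting list. The child, the parents and the therapist all know the group, so the blinded diagnostician is the main protection against expectation entering the score. An unblinding rule that names dropouts, in a plan that still rates dropouts, leaves a gap in that protection. An affected score could lean towards the group the rater expects to do better. The dataset would not show this unless someone recorded which ratings followed an unblinding.

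**Working it through.** **Step 1: who can be unblinded?** Therapists are open label and families are told their allocation. No other blinded party is named. The unblinding sentence therefore has one evident object, the diagnostician. This is an inference, because the sentence names nobody.

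**Step 2: is a dropout still rated?** Yes. All planned outcomes are to be assessed for dropouts, and the t1 CY-BOCS is one of them.

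**Step 3: does that rating count?** It can. The analysis uses available data, and nothing excludes a rating made after unblinding.

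**Step 4: is there a sequence that closes the gap?** None is stated. The text neither puts the rating before the unblinding nor provides a second blinded rater.

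**Step 5: is the unblinding needed?** The open-label therapist already knows the group. The article gives no reason why the diagnostician must also learn it when a child drops out.

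**Size.** Let f be the share of t1 ratings in each group made unblinded, and b the between-group rating bias among those ratings. The shift in the mean difference is f × b. The documents give neither f nor b.

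- *Ceiling for f.* The Subjects section enrols 30 and aims to analyse 20 per group, which leaves 30 − 20 = 10, and 10/30 = 33%. As a check, 20 / (1 − 1/3) = 30. This is not an estimate of f. Those 10 are the patients the plan expects not to analyse, and it does not say they all leave before t1.
- *Illustration only.* Assume 30 rated per group, no true effect, a two-sided t-test at 5%, and b in SD units (not from the documents).

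| b (SD) | Type I error, f = 10% | Type I error, f = 33% (ceiling) |
|---|---|---|
| 0.25 | 5.1% | 6.2% |
| 0.5 | 5.4% | 9.7% |
| 1.0 | 6.7% | 24.6% |

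With f = 0 it is 5.0%. The effect is slight if few ratings are affected and matters only if many are, so the actual count is needed.

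**Timing.** Trial status says no patients were included after December 2020. Adding 16 weeks puts the last t1 visits at about April 2021. Data preprocessing was to start in December 2021. Most t1 ratings were therefore probably complete when the article appeared.

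**Secondary: looks at the data.** The article allows preliminary results to be shown at conventions. It neither says the diagnostician sees them nor that the diagnostician is kept from them.

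**Secondary: visit mode.** At week 32 the treatment group has follow-up I, by teleconference, and the waiting group has its end-of-treatment assessment. If that assessment is also face-to-face, mode may reveal the group at that visit. The waiting group's mode is not stated.

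**The case against.** The strongest reply is that the sentence is a limit. It confines emergency unblinding to certain cases and does not say that each dropout is unblinded, still less before the t1 rating. The blind is restated in the randomisation paragraph, and a condensed article may leave the step-by-step procedure to the full protocol. This stands against reading the text as a rule that every dropout is rated unblinded. It does not remove the point, because the article itself names dropout as a ground and also requires dropouts to be rated.

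Three stronger readings are tempting, and the documents do not support them.

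- *A definite shift in CY-BOCS points, calculated from the 10 of 30 allowance.* This would need every planned dropout to be unblinded, rated and analysed, whereas the plan sets those patients aside as not analysed. Nor does anything show that the groups differ most among dropouts.
- *Type I error inflated by the convention presentations.* The article plans no interim analysis that might end the trial, so the error rate for repeated testing with early stopping does not apply. Nothing shows that the looks disclose any child's group to the rater.
- *Visit mode breaking the blind for the primary endpoint.* The possible contrast is at week 32, after t1 has been rated. No mode difference is described at t1.

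**Conclusion.** The point holds in a limited form. As written, the plan permits a dropout's t1 CY-BOCS to be rated by an unblinded diagnostician and used in the primary comparison. The conclusion rests on one sound inference, that the diagnostician is the person unblinded, and on the absence of any stated order between rating and unblinding. The size is unknown. It depends on how many t1 ratings followed an unblinding, which the sponsor can establish, and on a rating bias for which the documents give no figure. The sample-size reasoning is not affected. The convention looks are a minor related risk to rater expectancy. Visit mode is a remark about week 32 only.

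**What to change.** 1. **Rule.** Remove dropout as a ground for unblinding the diagnostician. Alternatively, state that the t1 CY-BOCS is rated before any unblinding.
2. **Ratings already made.** Before the group comparison is run, record which t1 ratings followed an unblinding. Report their number by group, and add a sensitivity analysis of the primary comparison without them. That analysis also removes selected patients, so read it beside the main result and not in place of it.
3. **Looks at the data.** Do not evaluate outcomes by group for presentations until t1 rating is complete, or state that such results are kept from the diagnostician.
4. **Week 32.** State the visit mode for each group. If the modes differ, note when reporting that visit that mode may have revealed the group.

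The cost is a change of wording, one recorded item per unblinded rating and one extra analysis. The only real loss is an early conference preview of group results. Item 1 protects only ratings still to be made, so item 2 carries most of the value at this stage.

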## Methods/design

### Subjects

The study has a parallel group design with an experimental group receiving treatment after baseline assessment and a waiting group receiving treatment after a waiting period of 16 weeks, comparably to the length of treatment. The planned allocation ratio is one expecting superiority in symptom reduction in the experimental group. Patients are recruited by licensed child and adolescent psychotherapists who work at the university hospital of Tübingen. A Google AdWords advertising and recruitment campaign is carried out in cooperation with the Department of Communication at the University Hospital Tübingen.

To deal with probable dropouts, we planned to enroll 30 children with OCD in the experimental group and 30 children with OCD in the waiting group with the aim to finally analyze 20 patients in each group. Including clinical considerations, this was a realistic sample size, we were able to achieve in a 3-year period. Sample size was planned according to the following considerations. As primary outcome, we considered the CY-Bocs score. Our primary assessment endpoint was the comparison at t1 post-treatment between the treatment and the waiting group. In the pilot study of our treatment protocol using a pre/post-assessment with *N* = 9 children with OCD [38], effect size was *d* = 2.02. Therefore, we knew, that our treatment protocol most likely will lead to symptom reduction. Effect size of another study comparing webcam-delivered CBT in 16 children with OCD with a waiting group of 15 children with an ANCOVA on post-treatment CY-Bocs scores, covarying baseline CY-BOCS scores, showed a significant effect of treatment with *η*^2^ = 0.36 [37]. A further study in adults with OCD [39], comparing face-to face exposure treatment (*n* = 20) with a waiting group (*n* = 16), revealed an effect size of *d* = 1.001 for the CY-Bocs comparison at post-treatment. Therefore, we estimated that the effect in our study as a comparison of CY-Bocs scores of an effective treatment in comparison to the waiting group at t1 will be high. We expected that there will be a significant difference comparing 20 patients with treatment with 20 patients in the waiting group at t1.

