All participants and their parents provide informed consent. On the consent form, participants are asked to allow the use of their data also for future projects of the department and the study team. The consent forms are available from the corresponding author on request. The trial does not involve collecting biological specimens for storage. Patients will be recruited through established OCD outpatient units in Tübingen and Cologne (Germany), OCD Society, the Clinic’s homepage, schools, Google AdWords, an interview with an influencer suffering from OCD, and local psychiatrists and psychologists in Tübingen.

After a telephone interview and a first visit at our research department in Tübingen to verify the suitability for taking part in the study, and the face-to-face diagnostic session, participants will be randomized to the experimental or waiting list groups. Inclusion criteria will be children and adolescents (aged between 6 and 18) with a primary diagnosis obsessive-compulsive disorder according to DSM-5, a CY-BOCS score higher than 16 and at least one primary caretaker, German-speaking (child & caretakers), and a family home equipped with a broadband internet connection. Psychiatric comorbidities are allowed as long as the comorbid disorder does not have a higher treatment priority than OCD. Participants are excluded if they have an IQ below 70, do not speak or understand German, have a psychiatric comorbidity or suicidality that makes participation clinically inappropriate, or if they should be treated in the hospital. Medication is allowed if treatment was stable for 6 weeks before inclusion into the study and will then be taken during the trial. Furthermore, patients will be excluded in case of drug addiction or if the family seems to be severely psychologically burdened such that participation in the sessions and support of the children during the trial will not be possible. This will also be discussed in the steering board of our study team. While participating in the study, no other psychological treatment is allowed. If reporting side effects, or if wished by the patients, the patients will be excluded from the study and transferred to another more appropriate therapy option.

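### The stated allocation procedure does not protect concealment: one envelope holds the whole ordered list, and a therapist from the team that screens families looks into it for each allocation

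*Protocol article*

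**What the plan says.** Under Study procedure and design, the protocol article says that a separate biometry institute produced a computer-generated list "with 8 blocks of 6 participants, consisting of" three waiting-group and three immediate-treatment places each. The list is kept in a cabinet, in a single sealed envelope. When a patient is allocated, a therapist belonging to the study team gives the family the result, and "For this purpose, the therapist looks into the sealed envelope containing the order of the randomization list".

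The same section has the study team, all psychotherapists, do the telephone eligibility screening. It adds that "The enquiries received by the study team by phone or email will then processed by the treating therapists", and that therapists are open label. Only the diagnostician is said to be kept unaware of the group.

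Some exclusion criteria under Subjects rest on judgement. Examples are a comorbidity or suicidality that makes participation clinically inappropriate, and exclusion "if the family seems to be severely psychologically burdened" to the point that taking part would not be possible. That last criterion is also discussed in the steering board of the study team.

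On timing, Subjects says that after a telephone interview, a first visit "and the face-to-face diagnostic session, participants will be randomized to the experimental or waiting list groups". Study procedure and design assigns patients "by block randomization according to the order of incoming calls". Later in the same paragraph it refers to the sequence of calls together with inclusion in the study, and it describes t0 as measured before randomization.

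**The concern.** Concealment means that nobody who can influence whether or when a family enters the trial can learn the next allocation. A biometry institute generating the list secures randomness, not concealment. What matters is how each allocation is released. Here it is released by consulting the whole ordered list, and the person consulting it belongs to the team that screens, encourages and excludes families.

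If the next slot is known, discretionary decisions can drift with it, consciously or not: how hard to encourage a hesitant family, or whether a burdened family is judged able to take part. There is a plausible motive, because one arm starts treatment at once and the other waits 16 weeks, and the article itself names timely access to expert therapy as what motivates families. The resulting imbalance could involve family support or motivation, which can affect the CY-BOCS at t1. A blinded rater would score such groups correctly and the comparison would still be biased. With 20 patients per group planned for analysis, each child carries 1/20 = 5% of a group mean, so a few steered inclusions could matter.

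**Working it through.** The article states no figure for concealment, so there is nothing to reproduce. The check sets the procedural statements side by side and then counts how much of the list can be foreseen.

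**Procedure**

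- Custody: one list in one envelope. No series of individual envelopes, central release or independent custodian is described, and looking up the order of the list is not release of one allocation at a time.
- Access: a therapist from the study team.
- Screening: the study team by telephone, with treating therapists processing enquiries.
- Discretion: judgement-based exclusions, one of them discussed in the team's own steering board.
- Oversight: weekly team meetings, no external supervision of the data and no trial auditing (Study procedure and design).

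**Predictability with the list open**

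- List length: 8 × 6 = 48 slots.
- Once the envelope has been opened for allocation k, 48 − k slots remain readable in advance.
- After the first opening (k = 1): 48 − 1 = 47, and 47/48 = 98%.

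**Predictability if the list had been hidden**

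This is an alternative to the case above, not an addition to it. It assumes that the block size and past allocations are known. A 3:3 block of 6 has C(6,3) = 20 equally likely orders. An allocation is certain once one arm has used its three places.

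| Position in block | Orders in which it is certain | Probability |
|---|---|---|
| 1, 2, 3 | 0 of 20 | 0 |
| 4 | 2 of 20 | 10% |
| 5 | 8 of 20 | 40% |
| 6 | 20 of 20 | 100% |

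- Expected certain allocations per block: 0.10 + 0.40 + 1.00 = 1.5, and 1.5/6 = 25%. Over the list: 8 × 1.5 = 12 of 48.
- Always guessing the arm with more places left gives 4.1 correct per block: 4.1/6 = 68.3%, or 8 × 4.1 = 32.8 of 48, against 50% for unpredictable allocation.

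**Timing**

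Read alone, the phrase on incoming calls would fix the slot at first contact. Three other statements point to a later moment: randomization after the diagnostic session (Subjects), the mention of inclusion alongside the call sequence, and t0 before randomization (both Study procedure and design). Consent is obtained during the diagnostic appointments. Most of the text therefore supports allocation after baseline, and the one sentence needs reconciling with it.

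**The case against.** The strongest reply is that several features limit the harm. An outside institute generated the list. A blinded diagnostician and a face-to-face session come before randomization. The main entry criteria rest on diagnosis or instruments (DSM-5 diagnosis, CY-BOCS above 16, IQ). The family-burden criterion goes to a board, not to one therapist. Tying the sequence to calls makes it harder to reorder families to fit a slot. All this stands and narrows the route to discretionary inclusion and encouragement. It does not close that route, because the board belongs to the study team and the diagnostician's blinding protects rating, not screening.

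A reader might infer more than the article supports:

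- That upcoming allocations were in fact known, or were used. The text shows only that they could be known.
- That the therapist who opens the envelope screened that same family. The text places both tasks in one team and does not say they fall to one person.
- That ineligible callers use up slots because assignment follows call order. This rests on one loosely worded sentence, and the other timing statements point the other way.

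It is also fair to say that the counts measure predictability, not bias. The 47 of 48 is a ceiling: it assumes that the first reader takes in and shares the whole list, and that enrolment fills it. The article gives no basis for converting it into CY-BOCS points.

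That a journal article condenses a fuller protocol is not a sufficient answer. The article describes the lookup explicitly, so the objection is to a stated mechanism and not to an omission.

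**Conclusion.** The concern holds at the level of the procedure. Followed as written, it leaves up to 47 of 48 allocations open to the screening team before inclusion, and fixed blocks of 6 would leave 25% certain even if the list were hidden. This rests on reading the single envelope and the single ordered list literally, and on the screening and allocating therapists sharing one team.

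Whether any inclusion was influenced is not shown, and the size of any bias in the t1 comparison cannot be estimated from the article. The timing statements are a matter for reconciliation, not evidence that allocation preceded eligibility. The weakness bears on the primary comparison, but Trial status says no patients were included after active recruitment ended in December 2020, so it can now be mitigated and disclosed but not removed.

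**What to change.** **Procedure.** Someone outside the screening and treating team, for example the biometry institute, should hold the list and release one allocation at a time, only after consent and the t0 CY-BOCS are recorded, with block sizes varied and not disclosed. The cost is one call or e-mail per patient. This applies to the plan as written and to any later trial using this procedure, but cannot be applied to patients already allocated.

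**Text.** Reconcile the sentence on incoming calls with Subjects and with the later mention of inclusion, stating that a slot is assigned only after consent and t0.

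**What can still be applied here:**

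- Make the primary t1 CY-BOCS comparison an ANCOVA with t0 CY-BOCS as covariate. Statistical analysis describes group-by-time ANOVAs and names the t1 comparison as most important, without naming a baseline covariate. The sample-size reasoning under Subjects already cites a study analysed by ANCOVA with this covariate. If an analysis plan not shown here already specifies this, it is enough to say so.
- Report who opened the envelope and when, relative to consent and t0, and report screening exclusions as far as records allow.
- Disclose inadequate concealment as a limitation, and say that adjustment for t0 CY-BOCS cannot remove selection on unmeasured factors such as motivation or family support.

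A test of t0 CY-BOCS against how predictable each allocation was is not worth adding. With the list open nearly every slot is equally predictable, so the test reduces to an ordinary baseline comparison, with little power at about 20 per group.

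The remaining cost is one covariate, a short factual account and a limitation statement. Trial status puts the start of data preprocessing at December 2021, and the covariate should be fixed before outcome data are analysed by group.
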